## Abstract

**Graphical Abstract:**

ISAR-DESIRE 5 Trial design overview. After classification of the predominant OCT restenotic pattern at the site of the MLA as either homogeneous or non-homogeneous, patients will undergo 1:1 randomization to receive either a DES or a DCB, using a stratified randomization approach. This unique design ensures balanced allocation of treatment modalities (DES or DCB) across the two OCT-defined restenotic patterns. DCB: Drug-Coated Balloon; DES: Drug-Eluting Stent; MLA: Minimum Lumen Area; OCT: Optical Coherence Tomography

[figure not shown]

**Supplementary Information:**

The online version contains supplementary material available at 10.1007/s12265-025-10650-x.

## Introduction

Despite significant advances in the percutaneous treatment of coronary artery disease (CAD), in-stent restenosis (ISR) remains the most common cause of revascularization failure following percutaneous coronary interventions (PCI) [1].

Indeed, although significantly less frequent than after bare-metal stent (BMS) implantation, the incidence of clinical drug-eluting stent (DES) ISR is up to 10% within the first 10 years after DES implantation [2].

ISR is strongly associated with patient and lesion complexity, and the proportion of complex patients has steadily increased over the years [3]. Hence, despite the improvements in PCI technology, the proportion of ISR is expected to increase in the coming years. This proportion, combined with the very high number of DES implanted around the world and its association with an increased risk of death and rehospitalization [3–5] makes ISR a clinical entity of strong public health significance [6].

In the last decade, with the advent of new-generation DES, this longstanding issue was believed to have been definitively solved. Indeed, randomized clinical trials have consistently documented a significant decrease in the risk of repeat revascularization with modern DES compared with earlier platforms [7–12]. Nevertheless, ISR continues to represent a clinical conundrum, since each intervention for ISR portends a higher risk for subsequent reintervention, with an increasing risk of recurrent ISR after treatment with DES or drug-coated balloons (DCB), particularly in presence of 3 metal layers [13, 14].

Several strategies for the treatment of ISR have been tested over the years [15], but DCB angioplasty and repeat DES implantation have emerged as the most effective options [16–20].

Guideline-writing authorities recommend DES over DCB for ISR treatment (Class I, Level A), mainly based on meta-analyses of trials published between 2013 and 2017, focusing on relative risk of recurrent revascularization [21]. Although expert guidelines support the use of intravascular imaging (IVI) for the management of ISR, a common limitation of all trials comparing treatments for ISR is the lack of systematic IVI assessment to evaluate potential advantages and/or drawbacks of different treatment strategies in specific IVI-defined ISR subsets.

As a result, it is still unclear how IVI findings may influence ISR treatment strategies.

Particularly, high-resolution IVI by means of intravascular optical coherence tomography (OCT) provides unique insights into the mechanisms leading to the occurrence of ISR, as well as the characteristics of restenotic tissue. According to such optical characteristics, restenotic tissue can be classified into several patterns, which have been shown to correlate with different histological substrates (Fig. 1) [22–24].

**Fig. 1 Fig1:**
[figure not shown]
Patterns of In-Stent Restenosis on Intravascular Optical Coherence Tomography and Corresponding Histological Substrates in the ISAR-DESIRE 5 trial. Tissue characterization will be performed at the frame of minimum lumen area. Based on its optical properties at intravascular OCT imaging, restenotic tissue has been subdivided into several patterns that correlate with different histological substrates. Previous histopathological validation studies of intravascular OCT findings have shown homogeneous patterns to consistently correlate with abundance of smooth muscle cells, whereas the remaining patterns are typically characterized by a multitude of histological findings. Aiming to apply a pragmatic, clinically oriented and easily applicable algorithm, restenotic tissue will be categorized as predominantly homogenous or non-homogenous. The latter category includes frame with prevalent heterogeneous, layered aspect and/or with neo-atherosclerosis. *: guidewire artifact. DES: Drug-Eluting Stent; MEM: Myxomatous Extracellular Matrix; OCT: Optical Coherence Tomography; SMC: Smooth Muscle Cells

These differing tissue patterns may impact the clinical outcomes of patients undergoing PCI for ISR in a way that is dependent on the treatment method (DES or DCB). However, the number of studies investigating such an hypothesis is very scarce, and to date, no prospective, randomized clinical data are available [25].

Against this background, this study aims to investigate the interaction between different OCT-defined tissue patterns and the relative efficacy of different interventional strategies (DES vs. DCB) in patients with ISR in a prospective, randomized fashion.

## Methods

Intracoronary Stenting And Restenosis – randomized trial of Drug-Eluting Stent Implantation or drug-coated balloon angioplasty according to neointima morphology in drug-eluting stent REstenosis 5 (ISAR-DESIRE 5, ClinicalTrials.gov: NCT05544864) is an investigator-initiated, multicenter, prospective, stratified, randomized controlled trial (RCT), designed to investigate a potential interaction between different restenotic tissue patterns and treatment modality (DCB or DES) of ISR lesions in patients presenting with DES-ISR.

The hypothesis being tested is that a significant interaction between OCT-defined tissue patterns (homogeneous or non-homogeneous) and treatment modality with the currently recommended ISR treatment strategies (DES or DCB) exists.

A total of 376 patients will be prospectively enrolled in Germany, Spain, and Belgium. The study started in September 2022 and is expected to conclude in 2026.

This trial will be conducted in accordance with the Declaration of Helsinki, ISO 14155, and applicable local laws and regulations. The protocol, amendments, and the subject's informed consent were approved by all participating sites'independent ethics committees (IEC).

Before enrollment in the study, investigators will inform patients orally and in writing about the scope, purpose, and possible risks/benefits of the study and his/her rights and duties in lay language. Signed informed consent must be collected before randomization. All patient data will be protected and anonymized by a specific identification code and entered into an electronic case reporting form (eCRF).

### Study Population

Patients ≥ 18 years old who have signed the written informed consent for participation in the study will be considered eligible for inclusion if they have ischemic symptoms and/or evidence of myocardial ischemia (including non-invasive or invasive functional tests), angiographic evidence of ≥ 50% diameter stenosis (visual estimation) in a native coronary vessel previously treated with DES, as well as availability of an OCT pullback of the target lesion. Key exclusion criteria are represented by cardiogenic shock, acute ST-elevation myocardial infarction (MI) within 48 h from symptoms onset, target lesion location in the left main coronary artery or in a bypass graft, or unsuccessful treatment of other lesion(s) during the same procedure. Multiple stent layers will not be considered an exclusion criterion. The complete list of inclusion and exclusion criteria is shown in Table 1.

**Table 1 Tab1:** Complete list of inclusion and exclusion criteria

**Inclusion criteria**
1) Age ≥ 18 years
2) Patients with ischemic symptoms and/or evidence of myocardial ischemia
3) Presence of ≥ 50% angiographic restenosis (visual estimation) after prior implantation of drug-eluting stents in native coronary vessels
4) Availability of an OCT-pullback of the target lesion
5) Written informed consent by the patient for participation in the study
**Exclusion criteria**
1) Cardiogenic shock
2) Acute ST-elevation myocardial infarction within 48 h from symptom onset
3) Target lesion located in left main or bypass graft
4) Additional coronary intervention planned within 30 days of the procedure
5) Non-successful treatment of other lesion(s) during the same procedure
6) Severe kidney disease (eGFR ≤ 30 ml/min/m^2^)
7) Contraindications to any components of the investigational devices or dual antiplatelet therapy
8) Pregnancy (present, suspected, or planned) or positive pregnancy test
9) Previous enrollment in the same trial or participation in any other study at the time of enrollment
10) Malignancies or other comorbidity conditions with a life expectancy of less than 12 months or that may result in protocol non-compliance
11) Patient’s inability to fully comply with the study protocol

*eGFR* estimated Glomerular Filtration Rate, *OCT* Optical Coherence Tomography

### Randomization and Study Procedures

Patients meeting all inclusion and none of the exclusion criteria will be considered eligible for participation in the study. Eligible patients will be randomized using an electronic randomization system in the chronological order in which they qualify. Patients will first be characterized during the procedure according to the OCT-defined restenotic pattern (homogeneous or non-homogeneous). Then, they will be randomized to either DES or DCB treatment in a 1:1 stratified way based on OCT-defined restenotic tissue in order to obtain an equal distribution of treatment modality within OCT patterns (Graphical Abstract). Patients randomized to repeat DES implantation will be treated with a permanent-polymer everolimus-eluting stent (Xience, Abbott Vascular), while those randomized to DCB angioplasty will undergo treatment with any CE-approved, commercially available DCB. Particular care will be paid to ensure optimal lesion preparation. It is strongly recommended to consider OCT findings when determining the PCI strategy (e.g.: choice of device size and length) (Supplemental Methods S1).

Additional lesions must be treated before the study lesion. In the case of multiple ISR lesions, the highest-grade ISR will represent the target lesion. Baseline clinical and interventional procedures will be performed according to standard clinical practice before randomization (Supplemental Methods S2 and Fig. 2).

**Fig. 2 Fig2:**
[figure not shown]
Scheduled activities during different periods of the ISAR-DESIRE 5 Trial. *: PCI will be performed only after randomization. †: Within 24 h after randomization. Hs: High sensitivity; OCT: Optical Coherence Tomography; PCI: Percutaneous Coronary Intervention

In the case of sub-occlusive ISR, precluding sufficient blood clearance through contrast medium and insufficient OCT image quality, lesion predilation with a 1.5 mm balloon will be performed to allow adequate vessel opacification and optimal OCT image quality.

A comprehensive description of peri-interventional and post-interventional therapies is provided in the Supplemental Methods S3.

### OCT Assessment

Real-time assessment of the intravascular OCT pullback will be performed by the operator in order to confirm the presence of ISR at the target lesion as well as to conduct qualitative characterization of restenotic tissue at the site of minimum luminal area (MLA) within the restenotic segment, which will ultimately guide stratification during the randomization process [25, 26].

The restenotic pattern will be defined as predominantly homogeneous (≥ 50% uniform optical proprieties that don’t show any focal variation in backscattering patterns) or non-homogeneous (focally changing optical properties with various backscattering patterns or a layered appearance) (Fig. 1). This classification was adapted from that originally proposed by Gonzalo et al. [24]. Detailed definitions are provided in the Supplemental Methods S4. Based on its optical properties at intravascular OCT imaging, restenotic tissue has been subdivided into several patterns that correlate with different histological substrates. Previous histopathological validation studies of intravascular OCT findings have shown homogeneous patterns to consistently correlate with an abundance of smooth muscle cells. In contrast, the remaining neointimal patterns are typically characterized by a multitude of histological findings, including myxomatous extracellular matrix, proteoglycans, organized fibrin and neoatherosclerosis [25–27]. Based on the findings of the aforementioned OCT-histology correlation studies and aiming to apply a pragmatic, clinically oriented, and easily applicable algorithm, restenotic tissue will be categorized as predominantly homogenous or non-homogenous.

Subsequently, a detailed offline analysis of OCT pullbacks, including morphometric measurements and qualitative tissue characterization, will be performed in a blinded way at the ISAResearch Center (German Heart Center, Munich, Germany), which will serve as the core laboratory for the present trial (Supplemental Figure S1). Following the enrollment of the first few patients, the core laboratory will provide feedback to participating centers on the qualitative tissue characterization.

### Patient Follow-up

Patients will be prospectively clinically monitored for endpoint-relevant clinical events throughout the study period. Furthermore, the concomitant medication will be reviewed. Patients will be clinically monitored daily during their in-hospital stay and contacted by phone or visited in-office at 30 ± 7 days, 12 months ± 30 days, and 24 months ± 30 days (Fig. 2).

### Study Endpoints

The primary endpoint of the study is represented by the composite of major adverse cardiac events (MACE) defined as all-cause death, MI, and target lesion revascularization (TLR) after 24 months of clinical follow-up. The prespecified secondary endpoints are represented by the individual components of the primary composite endpoint, target lesion failure (TLF), defined as a composite of cardiac death, target vessel MI and TLR, stent thrombosis (ST) according to the academic research consortium (ARC) criteria as well as the composite safety endpoint represented by of all-cause death and MI. Detailed definitions of the single endpoint components are provided in the Supplemental Methods S5.

### Statistical Analysis and Sample Size Calculation

According to current evidence, the incidence of homogeneous and non-homogeneous ISR patterns is comparable [25, 26], and thus, both arms are sized equally. We used a z-Test for the interaction effect of homogeneous morphology (yes/no) and stent treatment (yes/no) in a proportional hazard regression model. Based on the results of our previous explorative observational analysis [27], we assume a proportion of primary endpoint events of 12.5% in the group with non-homogeneous morphology and PCI with DES, of 40% in the group with non-homogeneous morphology and PCI with DCB and 27% in both groups (treated with DCB or DES) with homogenous morphology. With a power of 80%, a two-sided 5% significance level, and assuming a 25% drop-out due to patients lost to follow-up, the total estimated sample size of the study is 376 patients.

The analysis will be based on the intention-to-treat (ITT) population. The full analysis set (FAS) consists of all randomized patients. According to the ITT principle analysis, the FAS will allocate patients to treatment groups as randomized. The per-protocol (PP) population includes all patients of the FAS without protocol deviations. The primary endpoint will be analyzed using a Cox proportional hazards regression model, including the interaction effect of restenotic morphology (homogeneous vs. non-homogeneous) and treatment strategy (DES vs. DCB). Both factors will be included as binary (dummy-coded) variables. This approach will allow assessment of whether the effect of treatment differs according to the underlying OCT-defined restenotic morphology. The exploratory hypothesis of the primary and secondary endpoints will be performed similarly to the confirmatory analysis of the primary endpoint using ITT and PP populations. Event-times distribution will be estimated using the Kaplan–Meier method and tested for group differences by exploratory long-rank tests.

Descriptive statistics will be computed for baseline variables as appropriate.

Prespecified subgroup analysis will be performed for each of the following subgroups: age, sex, body mass index, diabetes mellitus, renal function, clinical presentation, angiographic classification of ISR, vessel size, and use of advanced lesion preparation devices (modified balloon, super-high pressure balloon, intravascular lithotripsy, and atheroablative techniques). Results will also be analyzed according to the OCT tissue appearance according to the central core lab analysis.

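### The primary Cox model is described without baseline covariates, forgoing a small gain in power, and stent layers, a plausible rival explanation for an interaction, appear nowhere in the described analysis

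*Protocol article*

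**What the plan says.** All references are to the protocol article.

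- **Model.** Statistical Analysis and Sample Size Calculation specifies a Cox proportional hazards model for the primary endpoint with the interaction of restenotic morphology and treatment strategy, and adds: "Both factors will be included as binary (dummy-coded) variables". No further model term is mentioned.
- **Sizing.** The sample size rests on the same test: "We used a z-Test for the interaction effect of homogeneous morphology (yes/no) and stent treatment (yes/no) in a proportional hazard regression model". The assumed event proportions are "12.5% in the group with non-homogeneous morphology and PCI with DES", "40% in the group with non-homogeneous morphology and PCI with DCB", and 27% in each homogeneous group. With 80% power, two-sided 5% and 25% drop-out, the total is 376.
- **Subgroups.** The prespecified list is "age, sex, body mass index, diabetes mellitus, renal function, clinical presentation, angiographic classification of ISR, vessel size", plus use of advanced lesion preparation devices.
- **Stent layers.** The Introduction says that the risk of recurrent restenosis after either device increases, "particularly in presence of 3 metal layers". Study Population states: "Multiple stent layers will not be considered an exclusion criterion". The Discussion counts additional layers among the main drawbacks of repeat DES. Layers are not mentioned in the model or the subgroup list.
- **Allocation.** Under Randomization and Study Procedures, patients are classified by OCT pattern and then randomised 1:1 to DES or DCB within pattern.

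**The concern.** Two separate matters are involved.

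**Efficiency.** In a time-to-event analysis, leaving out strong prognostic factors costs some power. Here the test is of an interaction with fewer than 100 expected events, and the candidate factors are being recorded anyway.

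**Attribution.** Treatment is randomised; tissue pattern is not. The interaction term therefore also picks up any baseline characteristic that both differs between patterns and changes the DES versus DCB effect. Number of existing stent layers is a natural candidate, because only one of the two devices adds a layer. If layers travel with pattern, a positive result could be credited to tissue morphology when stent history is responsible. The trial is meant to support imaging-guided choice of treatment, so readers will ask this question, and an answer produced only after the results are known will carry less weight.

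**Working it through.** **1. Reproduce 376 without covariates.** Inputs are the four event proportions, power, alpha and drop-out given above.

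- Interaction on the log hazard scale: ln[ln(1 − 0.125) / ln(1 − 0.40)] − 0 = ln(0.1335 / 0.5108) = −1.342, a ratio of hazard ratios of 0.261.
- Mean event proportion: (0.125 + 0.40 + 0.27 + 0.27) / 4 = 0.26625. Sum of 1/p: 8 + 2.5 + 3.704 + 3.704 = 17.907.
- n per cell = [1.960 × √(4 / 0.26625) + 0.842 × √17.907]² / 1.342² = 69.2, rounded up to 70.
- Drop-out: 70 / 0.75 = 93.3, rounded up to 94; 4 × 94 = 376.

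The article does not name its formula, so this is a match under one reasonable variant. Others give 350 (mean event rate throughout) or 417 (sum of 1/events throughout). The match shows that the planned size needs no covariate adjustment.

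**2. Power with and without a covariate.** Cox models were simulated with N = 376, 94 per cell and exponential 25% drop-out, with the 24-month proportions held at the planned values. The article gives no covariate effects, so those below are assumed.

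| Assumed covariate | Unadjusted | Adjusted | Gain (points) |
|---|---|---|---|
| Binary, 30% prevalence, HR 1.5 | 82.9% | 83.2% | 0.3 |
| Binary, 30%, HR 2 | 83.2% | 84.2% | 1.0 |
| Binary, 30%, HR 3 | 84.6% | 87.6% | 3.0 |
| Continuous, log HR 0.3 per SD | 82.9% | 84.2% | 1.3 |
| Continuous, 0.5 per SD | 84.8% | 87.5% | 2.7 |
| Continuous, 0.8 per SD | 86.6% | 91.1% | 4.5 |

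Binary rows use 2,500 runs and continuous rows 800. The standard error of one power figure is about 0.7 and 1.3 points respectively; the comparison within a row uses the same simulated data and is tighter. Unadjusted power exceeds 80% in every row.

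**3. Attribution.** Here pattern has no effect on the treatment contrast once the third factor is held fixed. The factor is commoner in non-homogeneous lesions. Entries are the median interaction coefficient (homogeneous × DES) and the rejection rate over 2,500 runs; the standard error at 5% is √(0.05 × 0.95 / 2,500) = 0.4 points.

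| Assumed factor | Two-factor model | + main effect | + factor × treatment |
|---|---|---|---|
| Prognostic only, HR 2, prevalence 40% vs 20% | 0.011; 5.6% | 0.014; 5.4% | 0.020; 5.4% |
| HR 1.5, modifies DES effect by 2, 40% vs 20% | −0.156; 6.8% | −0.165; 7.2% | 0.005; 5.1% |
| HR 1.5, modifies DES effect by 1/3, 50% vs 20% | 0.325; 11.4% | 0.325; 11.2% | 0.001; 4.9% |

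A purely prognostic imbalance does not shift the interaction. A factor that also modifies the treatment effect does. Adding its main effect leaves the shift in place; adding its product with treatment removes it. The largest shift, 0.325, is 0.325 / 1.342 = 24% of the planned interaction. The sign depends on which pattern has more layers and which device they favour, and the article settles neither.

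**The case against.** **The article is condensed.** It says that the interaction is included and how the two factors are coded; it does not say that nothing else enters. A covariate list may stand in the full protocol or SAP. This is fair: a reader might infer that the model is confirmed to hold only these terms, and the text does not go that far. The point is limited to the model as described, which is also the model used for sizing.

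**The interaction test is not confounded.** A reader might infer that it is. Randomisation within pattern makes DES versus DCB unbiased in each stratum, and the contrast of those two effects is a valid test of the stated hypothesis. In the scenarios with higher rejection rates, the treatment effect really does differ between patterns, through the third factor. Those rejections are not false positives for the trial's question, and a pattern could guide treatment whatever its cause. This stands in full. What remains is the explanation given to a positive result.

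**The layers scenario is assumed.** The Introduction describes risk after both devices, which is prognosis and not effect modification. The Discussion gives no modifying effect, and no passage ties layers to pattern. This also stands, so no size can be claimed. It does not remove the oddity that a factor stressed in three sections is absent from the described analysis.

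**Main-effect adjustment does not cure misattribution.** Correct; only the product term does, and the fix separates the two purposes.

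**Conclusion.** The point holds as a minor improvement in efficiency and interpretation.

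- **Efficiency:** main-effect adjustment for prognostic baseline factors would add about 0 to 5 points of power, depending on assumed covariate strength. A reader might infer that the trial is underpowered without it. The documents do not support that: 376 is reproduced with no covariate, and simulated unadjusted power runs from 82.9% to 86.6%.
- **Attribution:** a significant interaction could partly reflect a correlated effect modifier, and stent layers are a plausible candidate. Under assumed prevalences and modifying effects, the two-factor model rejected in 6.8% to 11.4% of runs when pattern itself had no role. If layers are unrelated to pattern or do not modify the treatment effect, the problem does not arise.

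Neither part invalidates the primary test.

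**What to change.** 1. Prespecify a short list of main effects in the primary Cox model: diabetes, angiographic ISR class, vessel size and number of stent layers (1 versus 2 or more, if recorded at baseline or read from the OCT pullback required for inclusion). Keep the two-factor model as a supportive analysis. Leave lesion preparation devices out of this list, since the schedule of activities places PCI after randomisation.
2. Add number of stent layers to the prespecified subgroups.
3. Prespecify one sensitivity model that adds a layers-by-treatment term, and report the pattern-by-treatment estimate with and without it.
4. Settle all of this before unblinded results are seen.

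**Cost.** This needs SAP wording and one baseline lesion variable. Under the planning rates with exponential drop-out, expected events are 94 × (0.109 + 0.352 + 0.236 + 0.236), about 88. If each added covariate takes one parameter, the primary model has 3 + 4 = 7, or about 12.6 events per parameter (88 / 7), and the sensitivity model has 8, or 11. The downside is that the hazard ratios become conditional on the covariates: with a binary covariate of HR 3, the median interaction coefficient moved from 1.342 to 1.411. The supportive two-factor model covers that.

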### Clinical Event Adjudication Committee

The Clinical Event Committee (CEC) will review and decide on all clinical endpoints. The CEC will create clear rules and processes for classifying a clinical event, using specific criteria based on the definitions in the study protocol. All committee members will be blinded to the randomized treatment assignments for all adjudicated patients.

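### The subgroup by use of advanced lesion-preparation devices is defined after randomisation, so DES-versus-DCB estimates within it are open to selection bias

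*Protocol article*

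**What the plan says.** The section Statistical Analysis and Sample Size Calculation lists nine prespecified subgroup factors. Eight describe the patient or the lesion: age, sex, body mass index, diabetes, renal function, clinical presentation, angiographic class of restenosis and vessel size. The ninth is "use of advanced lesion preparation devices (modified balloon, super-high pressure balloon, intravascular lithotripsy, and atheroablative techniques", which describes what the operator did.

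On timing, Randomization and Study Procedures has the restenotic pattern read on OCT during the procedure, and continues: "Then, they will be randomized to either DES or DCB treatment in a 1:1 stratified way based on OCT-defined restenotic tissue". The Fig. 2 legend adds that "PCI will be performed only after randomization".

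On how the lesion is to be prepared, the article says "Particular care will be paid to ensure optimal lesion preparation" and strongly recommends taking OCT findings into account in PCI strategy, with a pointer to Supplemental Methods S1, which is not shown.

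Blinding is stated in two places. For the event committee: "All committee members will be blinded to the randomized treatment assignments for all adjudicated patients". For the core laboratory, the offline OCT analysis "will be performed in a blinded way at the ISAResearch Center".

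**The concern.** A subgroup comparison keeps the protection of randomisation when membership is settled before allocation, or at least cannot be influenced by it. Here it is settled afterwards by someone who knows the allocation. An operator about to use a coated balloon may prepare the lesion differently from one about to implant a stent. If so, the DES and DCB patients who received these devices are different selections of lesions, and so are those who did not. A difference in MACE within either group would then mix treatment effect with lesion severity. Neither intention-to-treat allocation nor a treatment-by-subgroup interaction test repairs this.

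The trial aims at individualised choice between DES and DCB (Clinical Relevance). A prespecified result split by preparation device could therefore be read as evidence on which device suits which lesion, with more weight than its design supports.

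**Working it through.** The plan attaches no figure to this subgroup, so there is none to reproduce. The check has three parts.

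**1. Is the factor settled after allocation?**
- OCT classification comes first, then randomisation, then PCI (Randomization and Study Procedures; Fig. 2 legend). The listed devices are used during PCI.
- One sentence points the other way: "Baseline clinical and interventional procedures will be performed according to standard clinical practice before randomization". It is loosely worded, but the Fig. 2 legend places PCI itself after randomisation.
- The only ballooning of the target lesion described for obtaining an adequate OCT is in sub-occlusive restenosis: "lesion predilation with a 1.5 mm balloon will be performed to allow adequate vessel opacification and optimal OCT image quality". That is not one of the listed devices.
- The article does not use the term open-label. The operator's knowledge of the arm follows from the treatments themselves, and the stated blinding covers only the event committee and the core laboratory.
- The article gives no criterion that makes the choice of preparation device independent of the arm.

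**2. How large could the distortion be?** All inputs here are assumptions except the overall risk of 27%, which is the plan's rate for homogeneous lesions. The true hazard ratio is 1.00 throughout. The apparent hazard ratio (DES versus DCB) is ln(1 − risk in DES) / ln(1 − risk in DCB).

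*Model A, two lesion types.* Half the lesions are complex (24-month risk 40%) and half simple (14%), so the mean is 27%. Device use is given as simple / complex.

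| Scenario | DES use | DCB use | HR, users | HR, non-users |
|---|---|---|---|---|
| Same rule in both arms | 20% / 60% | 20% / 60% | 1.00 | 1.00 |
| Mild | 20% / 60% | 35% / 65% | 1.10 | 0.98 |
| Moderate | 15% / 60% | 50% / 70% | 1.24 | 0.93 |
| Strong | 10% / 60% | 70% / 80% | 1.38 | 0.89 |

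The mild row in full:
- DES users: (0.30 × 0.40 + 0.10 × 0.14) / 0.40 = 0.335.
- DCB users: (0.325 × 0.40 + 0.175 × 0.14) / 0.50 = 0.309.
- HR in users: ln(0.665) / ln(0.691) = 1.10.
- DES non-users: (0.20 × 0.40 + 0.40 × 0.14) / 0.60 = 0.227.
- DCB non-users: (0.175 × 0.40 + 0.325 × 0.14) / 0.50 = 0.231.
- HR in non-users: ln(0.773) / ln(0.769) = 0.98.

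*Model B, continuous severity.* By simulation, a device is used when severity plus random noise exceeds an arm-specific threshold. The log hazard rises by 0.4 to 0.7 per SD of severity.

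| Use, DCB vs DES | Noise SD | HR, users | HR, non-users |
|---|---|---|---|
| Equal | any | 1.00 | 1.00 |
| 55% vs 45% | 0.5 to 2 | 1.03–1.11 (both groups) | as users |
| 60% vs 40% | 0.5 | 1.12–1.20 | 1.13–1.24 |
| 60% vs 40% | 1 | 1.09–1.15 | 1.10–1.18 |
| 60% vs 40% | 2 | about 1.05–1.10 (both groups) | as users |
| 70% vs 30% | 0.5 | 1.25–1.45 | 1.28–1.55 |
| 70% vs 30% | 1 | 1.19–1.34 | 1.21–1.40 |

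The models disagree on non-users. In model A the extra DCB use falls mainly on simple lesions, which leaves relatively more complex lesions among DCB non-users. In model B it falls on the next most severe lesions, so DCB non-users are milder. The document does not say which pattern, if either, applies.

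**3. How does this compare with sampling error?** The plan's mean risk is (12.5 + 40 + 27 + 27) / 4 = 26.6%, so 376 patients give about 100 events before losses. If half fall in each subgroup level, that is about 50 events. The standard error of the log hazard ratio is then about √(4/50) = 0.28, and the 95% interval extends by a factor of about exp(1.96 × 0.28) = 1.7 each way.

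**The case against.** The strongest reply is that nothing in the article says preparation differs by arm. The call for careful preparation is not arm-specific, the recommended guide to strategy is an OCT obtained before randomisation, and Supplemental Methods S1 may standardise the choice. If the lesion alone determines the device, there is no bias of this kind. That stands. A reader might infer that the subgroup estimates are biased, or that they would wrongly favour one device in both users and non-users. The documents support neither: they show only that the comparison is unprotected.

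The hazard ratios rest on assumed use rates, severity effects and, in model B, a noise term that moves the result considerably. That also stands, which is why the range starts at 1.00.

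The consequence is limited. This is one of nine subgroup factors, no confirmatory claim attaches to it, and the milder distortions lie well inside its sampling error. That bears on the priority of the point. It does not remove it, because selection bias does not average out and is not reflected in the confidence interval.

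It may be said that handling of subgroups belongs in an analysis plan that is not shown. Interpretation may. But the choice of factor is fixed in the article, and the timing problem follows from that choice.

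Finally, not every other factor is demonstrably a baseline one: the article does not say when or how vessel size is measured. The contrast drawn here is only that device use is an operator's action taken after allocation.

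**Conclusion.** The point holds in a limited form. As listed, the subgroup rests on a factor settled after randomisation by an operator who knows the arm, so DES-versus-DCB estimates among users and non-users are open to selection bias. Whether bias arises, how large it is and which way it runs cannot be derived from the document. With a true hazard ratio of 1.00 and the assumptions above, the apparent value is 1.00 if use does not depend on the arm, about 1.03 to 1.25 under mild dependence and about 1.5 at the strong end. In non-users it may lie below 1 (0.98 to 0.89 in model A).

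A reader might extend the criticism to the main result. That would be wrong: the primary test concerns an OCT pattern classified before randomisation and does not involve this factor. The item should be changed, but it does not threaten the trial's conclusion.

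**What to change.** Take the use of these devices off the list of treatment-effect subgroups and report it by arm descriptively, which also shows whether use differed between arms. If outcomes are still compared by device actually used, label that comparison non-randomised and exploratory. If the real question is whether lesion complexity modifies the treatment effect, define the subgroup by angiographic or OCT features recorded before randomisation, and fix the definition before outcomes are examined by arm.

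The cost is about one line in the protocol or analysis plan and no additional patients. One prespecified subgroup loses its randomised interpretation, and the substitute works only if suitable baseline features were captured. Recording the operator's intended preparation before randomisation would also give a valid factor. However, it needs a new eCRF field and cannot be done for patients already enrolled since September 2022.
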